# Impact of COVID-19 Pandemic Burnout on Cardiovascular Risk in Healthcare Professionals Study Protocol: A Multicenter Exploratory Longitudinal Study

**DOI:** 10.3389/fmed.2020.571057

**Published:** 2020-12-22

**Keywords:** COVID-19, burnout—professional, cardiovascular risk (CV risk), immune dysfunction, healthcare professional

## Abstract

**Introduction:** The coronavirus disease 2019 (COVID-19) pandemic has created new and unpredictable challenges for healthcare systems. Healthcare professionals are heavily affected by this rapidly changing situation, especially frontline healthcare professionals who are directly engaged in the diagnosis, treatment, and care of patients with COVID-19 and may experience psychological burdens. The objective of this study is to explore the evolution of psychosocial, cardiovascular, and immune markers in healthcare professionals with different levels of exposure to the COVID-19 pandemic.

**Methods and Analysis:** This is a STROBE compliant, blended, exploratory study involving online and onsite approaches that use wearable monitoring. A planned random probability sample of residents, staff physicians, nurses, and auxiliary healthcare professionals will be recruited. The study sample will be stratified by exposure to the COVID-19 pandemic. As a first step, recruitment will be conducted online, with e-consent and using e-surveys with Maslach Burnout Inventory, Fuster-BEWAT score, and sociodemographic characteristics. Onsite visits will be planned for the second step where participants will receive a wearable setup that will measure heart rate, actimetry, and sleep quality monitoring, which will be used together with blood sampling for immune biomarkers. Steps 1 and 2 will then be repeated at 2–3 months, and 6 months. Power BI and Tableau will be used for data visualization, while front-end data capture will be used for data collection using specific survey/questionnaires, which will enable data linkage between e-surveys, internet of things wearable devices, and clinical laboratory data.

**Clinical Trial Registration:**
ClinicalTrials.gov; Identifier: NCT04422418

## Introduction

The coronavirus disease 2019 (COVID-19) pandemic has created new and unpredictable challenges for healthcare systems. Healthcare professionals are heavily affected by this rapidly changing situation (1). Common challenges faced by all healthcare modalities during the pandemic include limited expert staff availability and the risk of the peri-procedural transmission of SARS-CoV-2 between patients and staff (2). Managing the unpredictable scenario of the COVID-19 pandemic caused an unprecedented challenge for healthcare leadership to promptly act to reorganize and provide the critical resources and information workforce needed to manage this health crisis. Recommendations on precautions, indications, prioritization, and protection are continuously updated for patients and healthcare professionals (1, 2).

The COVID-19 pandemic has caused striking increases in the prevalence of symptoms of depression, anxiety, and burnout in clinicians and other healthcare professionals (3). Physician burnout is already a significant problem in the healthcare industry (4). Working stress and burnout can lead to chronic symptoms of exhaustion and ultimately to an increased risk of cardiovascular disease (5). The total occupational burden has also been related to cardiovascular risk in physicians (6). For instance, medical occupational risk factors such as stress and adverse psychosocial working conditions can increase cardiovascular disease (7). Increased risk of cardiovascular morbidity and mortality have been identified by alterations in cardiac autonomic function that can be assessed by cardiac variability (HRV) (8). Recent findings suggest that the measurement of HRV can be applied in occupational settings to assess burnout (5). According to Lo et al., measuring HRV “not only allows administrators to quickly select the colleagues who need health care but also provides timely and appropriate care, thereby promoting the health of the worker” (5). Cardiovascular risk is not only increased by work-related stress in healthcare, the immune system can also become deficient (9). Immunological biomarkers have been reported to be associated with job-related stress (10). A single-item global job satisfaction measure may be a valid tool to evaluate immune status in healthy white-collar employees (11).

As Dzau, Kirch, and Nasca discuss in a report on preventing this parallel pandemic, “the surge of physical and emotional harm that amounts to a parallel pandemic, […] there has never been a more important time to invest in the clinician workforce. We have a brief window of opportunity to get ahead of two pandemics, the spread of the virus today and the harm to clinician well-being tomorrow. If we fail, we will pay the price for years to come. In the race to respond to the Covid-19 crisis, we must not neglect to care for those who care for us” (12).

## Aims and Objectives of the Study

The purpose of this project is to explore the development of psychosocial, cardiovascular, and immune markers in healthcare professionals with different levels of COVID-19 exposure. The effects of the pandemic work burden on psychological, cardiovascular, and immune markers will be stratified per level of exposure to the COVID-19 pandemic, diagnostic to COVID-19, profession, sex, age, and already existent cardiovascular risk.

The objectives of the study are: (I) to evaluate the level of burnout and cardiovascular health between frontline and second-line healthcare professionals; (II) to identify the effect of healthcare professional category (residents, staff physicians, nurses, and auxiliary staff) and the number of years of experience in relation to the possible associations between burnout and cardiovascular and immune biomarkers; and (III) to explore the association between burnout and cardiovascular and immune biomarkers in frontline and second-line healthcare professionals in multivariable linear regression models, adjusted for relevant confounding variables, including information on socio-demographic, anthropometric, and traditional CVD risk factors.

## Methods

### Ethics

Electronic informed consent (e-Consent) will be obtained through the initial study recruitment email before the participants complete the online questionnaires (13, 14). Written informed consent will be obtained in the second step of the study (Figure 1) when eligible participants will be verbally informed by trained research personnel about the nature and purpose of the study, and the use of wearable technology for data collection. All participants will be made aware of the fact that they can withdraw from the study at any time without penalty.

**Figure 1 F1:**
[figure not shown]
Covid-19 study flow chart.

### Design

This is an exploratory observational cohort study. The STROBE and The EQUATOR Network were followed in the design of the protocol of this study (15). The study is designed to capture the phenotyping of participants in the areas of psychosocial, cardiovascular, and immune markers profiles, and healthcare usage data linkage.

### Setting

Hospitals in the United Arab Emirates.

### Inclusion and Exclusion Criteria

Participants will be recruited from public hospitals in the UAE. The study has a recruitment goal of 200 residents, staff physicians, nurses and auxiliary healthcare professionals (adult males and females over 18 years) from both inpatient and outpatient medical services will be assessed at baseline, 3 months, and 6 months with a single outcome assessor (Figure 1). A follow-up protocol for participants will be applied to minimize missing data to <20%.

Inclusion criteria are that all residents, staff physicians, nurses, and auxiliary healthcare professionals from both inpatient and outpatient medical services who agree to be part of the study will be provided with heart rate tracking devices to monitor heart rate.

Exclusion criteria will be that participants are not willing to complete the written consent form.

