### Sample Size

Our study initially explored the ideal sample size based on consideration of the feasibility of recruitment, costs, and logistics. After an initial evaluation, a minimum recommended sample size of 270 healthcare professionals was determined to be valid by Rao Soft® sample size calculator at a 90% power and 5% margin of error. The sample size was 220 when calculated with G^*^Power 3.1.9.6 for Mac OS X G^*^Power 3, an analysis program for the social, behavioral sciences (19), considering an effect size w = 0.3, α err prob = 0.05, power (1-β err prob) = 0.95. To minimize the possibility of attrition bias, we ensured good communication between site principal investigators and participants with personalized invitations (20).

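### The recruitment goal of 200 is below both derived sample sizes (220 and 270), and neither allows for missing data, so the stated power and margin do not describe the study as sized

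*Protocol article*

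**What the plan says.** Three numbers are given for the size of the study.

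- Inclusion and Exclusion Criteria: "The study has a recruitment goal of 200 residents, staff physicians, nurses and auxiliary healthcare professionals". They are assessed at baseline, 3 months and 6 months.
- Sample Size, first figure: "a minimum recommended sample size of 270 healthcare professionals was determined to be valid". It came from a web "sample size calculator at a 90% power and 5% margin of error".
- Sample Size, second figure: "The sample size was 220 when calculated with" G*Power, "considering an effect size w = 0.3, α err prob = 0.05, power (1-β err prob) = 0.95".

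On missing data, the Inclusion and Exclusion Criteria section says "A follow-up protocol for participants will be applied to minimize missing data to <20" per cent, and the Data Collection and Assessments section repeats this. The Sample Size section answers attrition only with "To minimize the possibility of attrition bias, we ensured good communication between site principal investigators and participants with personalized invitations".

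The Discussion adds that the sample was not chosen to power a specific primary hypothesis and that the study should be regarded as exploratory.

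**The concern.** The target is lower than a figure that the protocol itself calls a minimum, and lower than the figure it ties to power 0.95. The number 200 does not appear in the Sample Size section. That section mentions feasibility, cost and logistics as a starting consideration, but what follows from that evaluation is 270, not 200. A reader cannot tell which number governs or when recruitment is complete.

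The stated power and margin belong to 220 and 270, not to 200. They fall further if a fifth of participants lack 6-month data, because no figure carries an allowance for that. Results from 200 people could then be cited as having a power or precision that 200 does not give. The Discussion also expects other institutions to use this protocol, and they would inherit three incompatible sizes.

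**Working it through.** **Inputs from the article:** target 200; derived sizes 220 and 270; w = 0.3, alpha = 0.05, power = 0.95; margin 5%; missing data below 20%. **Not stated, so assumed:** the df of the chi-square test, and the response proportion and population size behind 270.

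**Step 1: reproduce 220.** The effect size w belongs to the chi-square family. Power is the probability that a noncentral chi-square variable with noncentrality N × w² exceeds the 5% critical value. The smallest N with power 0.95 at w = 0.3 is:

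| df | 1 | 2 | 3 | 4 | 5 | 6 |
|---|---|---|---|---|---|---|
| N | 145 | 172 | 191 | 207 | 220 | 232 |

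Only df = 5 gives 220 (noncentrality 220 × 0.09 = 19.8, power 0.950). It contains no dropout allowance.

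**Step 2: reproduce 270.** n = z² × p(1 − p) / e², with p = 0.5 and e = 0.05.

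- 90% confidence: 1.645² × 0.25 / 0.0025 = 270.6; with a finite-population correction at a population of 100,000, 269.8.
- 95% confidence: 384.

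So 270 is a precision calculation at 90% confidence, although the text calls the 90% a power. It too contains no dropout allowance.

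**Step 3: what the target delivers.** With 20% missing, 200 × 0.8 = 160 and 220 × 0.8 = 176. The margin is 1.645 × √(0.25 / N).

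| N | Power (w = 0.3, df = 5) | Margin at 90% confidence |
|---|---|---|
| 270 | 0.982 | 5.0 points |
| 220 | 0.950 | 5.5 points |
| 200 | 0.927 | 5.8 points |
| 176 | 0.887 | 6.2 points |
| 160 | 0.850 | 6.5 points |

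The w detectable with power 0.95 at df = 5 is 0.314 with 200 and 0.352 with 160. The confidence attached to a 5-point margin is 84% with 200 and 79% with 160.

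**Step 4: sensitivity to the assumptions.**

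- *Degrees of freedom.* Power at w = 0.3 with 200 and with 160 is 0.989 and 0.967 for df = 1, 0.975 and 0.935 for df = 2, and 0.959 and 0.905 for df = 3. For these tests 200 exceeds 0.95, but the derived size would then have been 145, 172 or 191, not 220.
- *Population size.* With a finite-population correction, 200 gives 5 points at 90% confidence only if the population is about 764 or fewer: 200 × (270.55 − 1) / (270.55 − 200) = 764. That does not fit a derived size of 270.

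**Step 5: what an allowance would look like.** Dividing by 0.8, 220 becomes 275 and 270 becomes 338. This shows that the allowance is absent; it is not a call to enrol more.

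**The case against.** The best defence is that the study is exploratory and says so. The Discussion disclaims a powered primary hypothesis, so readers are told not to weigh a null result against a nominal power. This stands as a limit on the harm. It does not say how many people will be enrolled, and it sits awkwardly beside a calculation at power 0.95.

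Second, the loss is small before attrition: 0.927 against 0.95, and 5.8 points against 5. The figures at 160 need the full 20% to be lost, whereas the plan aims for less. They also apply only to complete-case follow-up analyses; a baseline analysis can use up to 200. All of this stands.

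Third, the power shortfall rests on a df that is inferred. That is true, but it is the only df that yields the printed 220, and the margin shortfall does not depend on it.

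A reader might go further and infer that the frontline versus second-line comparison is underpowered. The documents do not support that. A two-group comparison has df = 5 only if the outcome has six categories. With a binary outcome (df = 1), power at w = 0.3 is 0.989 with 200 and 0.967 with 160. Nor does w describe the multivariable linear regressions planned for the third objective, so these figures say nothing about their power.

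**Conclusion.** The point holds as an inconsistency in the stated sample size. The goal of 200 is below both derived sizes, nothing reconciles them, and neither allows for the missing data that the plan tolerates. The stated power of 0.95 and margin of 5% therefore do not describe the study as sized. On the protocol's own inputs the study has 0.93 and 5.8 points at enrolment, and 0.85 and 6.5 points with about 160 complete at 6 months.

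The power figures assume a chi-square test with df = 5, back-solved from 220. The margins assume 90% confidence, a proportion of 0.5 and a large population, back-solved from 270.

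A reader might also infer that 220 and 270 were miscalculated, or that the study must recruit more. Neither follows: both figures reproduce, and an exploratory study of 200 is defensible if it reports the properties of 200.

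**What to change.** State the same single target in the Inclusion and Exclusion Criteria and Sample Size sections, with the number expected to be evaluable at 6 months. If 200 stands:

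- Present 270 and 220 as sizes that were calculated but not adopted, give the reason, and stop calling 270 a minimum.
- Restate what 200 enrolled and about 160 evaluable deliver: power 0.93 and 0.85 for w = 0.3, and margins of 5.8 and 6.5 points. Name the test, the df and the confidence level so that the figures can be checked. The authors should confirm that df = 5 was the setting used; if not, the power must be recomputed.
- Correct 90% power to a 90% confidence level, if that was the calculator setting.
- Cross-refer to the exploratory statement in the Discussion, so that the power figures are not read as support for a primary hypothesis.

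The cost is a rewording of these paragraphs and slightly less favourable stated figures. No extra participants are needed.

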### Recruitment

Potential participants in the study will be recruited through institutional mass email, which will be sent by either a campus office or the researcher (16). The study uses random probability sampling with each population member having a non-zero chance of being selected. In order to increase response rates and facilitate confidentiality, the anonymity of data, and e-consent in participants, it will be necessary to identify recruitment researchers through electronic surveys (17). Since our study is sponsored by academic and governmental agencies, we expect to have good response rates for mass email recruitment (18). Electronic surveys are a widely used method of collecting data in an efficient and timely manner (17), which will facilitate the Maslach Burnout Inventory, the Fuster-BEWAT score, and the accuracy of the sociodemographic characteristics gathered.

### Sample Size

Our study initially explored the ideal sample size based on consideration of the feasibility of recruitment, costs, and logistics. After an initial evaluation, a minimum recommended sample size of 270 healthcare professionals was determined to be valid by Rao Soft® sample size calculator at a 90% power and 5% margin of error. The sample size was 220 when calculated with G^*^Power 3.1.9.6 for Mac OS X G^*^Power 3, an analysis program for the social, behavioral sciences (19), considering an effect size w = 0.3, α err prob = 0.05, power (1-β err prob) = 0.95. To minimize the possibility of attrition bias, we ensured good communication between site principal investigators and participants with personalized invitations (20).

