One potential limitation of the present study is that the sample size was not selected to power a specific primary hypothesis and therefore should be considered as exploratory. As on-site visits to hospitals are planned for the second stage of the study protocol, difficulties may arise due to the regulations imposed by the pandemic. Another potential challenge could be due to the fact that the participants in the study may have reservations about the wearable devices, including worries about geophysical tracking data. In order to prevent such difficulties, recruiters will be specially trained to follow the requirements enforced by the pandemic and to provide the participants with sufficient clarifications regarding the study and the equipment used.

Considering the necessary physical and social distancing during a pandemic, internet- and smartphone- technology therapies or preventive measures can be used as an effective intervention or prevention in people with resilience or occupational stress.

The internet could be exploited for telemedicine and restoring daily routines, online platforms may be used to monitor the toll of the pandemic on mental and cardiovascular health (38).

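### The 270 figure is labelled as having 90% power, but it reproduces as 90% confidence for one proportion within 5 points, so that calculation establishes no power for any group comparison

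*Protocol article*

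**What the plan says.** The Sample Size section of the protocol article gives two calculations. The first yields "a minimum recommended sample size of 270 healthcare professionals", from a "sample size calculator at a 90% power and 5% margin of error". No null value, alternative, significance level, test, group split, assumed proportion or population size accompanies it.

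The second is a conventional power calculation: "The sample size was 220 when calculated with G^*^Power 3.1.9.6", "considering an effect size w = 0.3, α err prob = 0.05, power (1-β err prob) = 0.95".

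Three other places bear on the point:
- **Aims and Objectives of the Study.** Objective I is "to evaluate the level of burnout and cardiovascular health between frontline and second-line healthcare professionals".
- **Inclusion and Exclusion Criteria.** "The study has a recruitment goal of 200 residents", with the other staff groups listed after it.
- **Discussion.** As a limitation, "the sample size was not selected to power a specific primary hypothesis and therefore should be considered as exploratory".

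**The concern.** Power is a property of a test: it needs a null, an alternative and a significance level. A margin of error is the half-width of an interval and goes with a confidence level. The sentence on 270 attaches power to a margin of error, which such a calculation cannot have.

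The word cannot be passed over as loose usage. The next sentence uses power in its technical sense, as one minus the type II error, for the 220. Read together, the two sentences look like two power calculations, at 90% and 95%, when only the second is one. Someone who takes the label literally could credit the study with 90% power for its group comparisons on the strength of a calculation about a single overall proportion.

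**Working it through.** **Inputs from the document.** n = 270, 90% and 5 points; w = 0.3, alpha = 0.05, power 0.95 and n = 220 (all Sample Size). Recruitment goal 200 (Inclusion and Exclusion Criteria).

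**Assumptions, not in the document.** Proportion p = 0.5, a large population and simple random sampling for the 270; 5 degrees of freedom for the 220.

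**1. Reproduce 270 as a confidence-level calculation.** n = z² p(1 − p) / e², with z = 1.645 for 90% two-sided confidence:

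n = 1.645² × 0.25 / 0.05² = 270.55 (with unrounded z)

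That is 270 truncated. With the finite-population correction n / (1 + (n − 1)/N), it is 269.8 for N = 100,000, 267.0 for N = 20,000 and 263.5 for N = 10,000.

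**2. Try 90% as power to detect 5 points.**

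| Reading (50% versus 55%, alpha 0.05) | n needed |
|---|---|
| One sample, two-sided | about 1,047 |
| One sample, one-sided | about 853 |
| Two equal groups, two-sided | 2 × 2,095 = 4,190 |

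For the first row: (1.96 × 0.5 + 1.2816 × √(0.55 × 0.45))² / 0.05² ≈ 1,047. None of these is near 270.

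**3. Try 95% confidence.** 1.96² × 0.25 / 0.05² = 384. To reach 270 at 95% needs a population of about 901 to 911, or p of about 0.23 in a large population. Neither matches the printed 90%.

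**4. Check the separate power calculation.** For a chi-square test the noncentrality is N w². At N = 220 it is 220 × 0.09 = 19.8, and with 5 degrees of freedom and alpha 0.05 the power is 0.950; 220 is the smallest N that reaches 0.95. With the same inputs, N = 270 (noncentrality 24.3) gives about 98% and N = 200 (noncentrality 18.0) about 93%.

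**5. Precision at the recruitment goal.** For one proportion, under the assumptions of step 1:

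1.645 × √(0.25 / 200) = 0.058, or about 5.8 points at 90% confidence.

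**6. Illustration for a two-group contrast.** This further assumes a binary outcome near 50% and two equal groups, neither of which the article defines. The 90% half-width for the difference at 100 per group is 1.645 × √(0.5 / 100) = 0.116, or about 11.6 points.

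**The case against.** The strongest reply is that the slip is verbal and largely defused. The Discussion says plainly that the sample was not chosen to power a specific primary hypothesis, and the study is called exploratory throughout. A reader looking for a power statement finds a proper one in the next sentence. The 270 is not the recruitment target either, so relabelling it changes no endpoint, analysis or enrolment figure. All of this stands and lowers the consequence. It does not make the printed 90% power correct, and the Discussion's limitation sits awkwardly beside it.

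Three stronger readings are tempting, and the document does not support them:
- A reader might infer that 270 people would have no power for any comparison. That does not follow. With the article's own w = 0.3 and alpha 0.05, and the 5 degrees of freedom that reproduce 220, 270 people would have about 98% power. That power comes from the second calculation's inputs, not from the one that produced 270.
- A reader might treat the between-group half-width as the study's true precision. The outcomes listed are an inventory, a score, heart rate variability indexes and biomarkers. No binary endpoint and no frontline/second-line split is fixed, and the article never claims 5 points for a difference.
- A reader might fault the choice of 90% over 95% confidence. That is a choice, not an error.

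**Conclusion.** The label is wrong as written. On the stated 90% and 5 points, 270 is the size needed to estimate one proportion within 5 points at 90% confidence (270.55), and no power reading tried comes close (853 to 4,190). This calculation establishes no power for the frontline versus second-line comparison or any other; the only power calculation in the section is the one for 220.

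The identification rests on p = 0.5, a large population and simple random sampling. The article states none of these: it describes random probability sampling and stratification by exposure. Only the authors can confirm what they entered. That a margin of error has no power does not depend on these assumptions.

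The precision is also not reached at the size to be recruited: about 5.8 points at 200, under the same assumptions. Because the article discloses that it is exploratory and not powered for a primary hypothesis, the severity is moderate: worth correcting, but not a condition for the study to proceed.

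**What to change.** In the Sample Size section:
- Replace the reference to 90% power with a 90% confidence level for estimating a single proportion.
- Have the authors state the proportion and population size they entered. The values assumed here should not be written in as fact.
- Say that this figure implies no power for group comparisons.
- Give the precision at the recruitment goal of 200: about 5.8 points at 90% confidence if p = 0.5 and the population is large, or the figure that follows from the authors' actual inputs.
- If a between-group precision is added, such as about 11.6 points at 100 per group, mark it as an illustration that assumes a binary outcome near 50% and equal groups.

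The cost is a few sentences. The relabelling itself changes no recruitment, assessment or analysis; it replaces a more favourable claim with an accurate one.

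### The 95% power quoted for 220 participants is for a chi-square effect size with no test or degrees of freedom named; it does not carry over to the linear regression, the only analysis the article names

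*Protocol article*

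**What the plan says.** All references are to the protocol article.

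- **Sample Size** gives two figures. One is "a minimum recommended sample size of 270 healthcare professionals was determined to be valid by Rao Soft® sample size calculator at a 90% power and" a 5% margin of error. The other comes from G*Power: "The sample size was 220 when calculated with" that program, "considering an effect size w = 0.3, α err prob = 0.05, power (1-β err prob) = 0.95". No test, degrees of freedom, endpoint or allowance for dropout accompanies the 220.
- **Inclusion and Exclusion Criteria** sets a different number: "The study has a recruitment goal of 200 residents, staff physicians, nurses and auxiliary healthcare professionals". It also aims to keep missing data below 20%.
- **Aims and Objectives of the Study** names a method for objective III only. Associations between burnout and the cardiovascular and immune biomarkers are to be explored "in multivariable linear regression models, adjusted for relevant confounding variables". Objectives I and II name no test.
- **Discussion** lists as a limitation that "the sample size was not selected to power a specific primary hypothesis and therefore should be considered as exploratory".

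**The concern.** Power belongs to a particular test against a particular alternative. Cohen's w measures departure from the null in a chi-square test on counts. It is not the effect size for a coefficient in a linear regression, where f² or the partial correlation is used. The article attaches 95% power to w and then names linear regression as its analysis. Several of its outcomes are continuous: heart rate variability indexes, C-reactive protein and cortisol.

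The stake is how a null result would be read. The findings are to go to policymakers. If burnout shows no association with a marker, a reader holding the 95% figure could take that as good evidence of no association. The figure gives no such assurance for the regression, because no regression effect size was specified. The Discussion's disclaimer points the other way, so it is unclear how much weight the calculation should bear.

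**Working it through.** **1. Reproduce 220.** Inputs from the Sample Size section: w = 0.3, "α err prob = 0.05", "power (1-β err prob) = 0.95". The df are not stated, so they are scanned.

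Formula: power = P(χ²(df, λ) > c), where λ = N × w² = 0.09N and c is the 95th percentile of the central chi-square with the same df. For N = 220, λ = 0.09 × 220 = 19.8. At 5 df, c = 11.07 and the power is 0.9502.

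| df | N for 95% power | Power at 220 | Power at 200 | Power at 160 |
|---|---|---|---|---|
| 1 | 145 | 99.4% | 98.9% | 96.7% |
| 2 | 172 | 98.4% | 97.4% | 93.5% |
| 3 | 191 | 97.4% | 95.9% | 90.5% |
| 4 | 207 | 96.2% | 94.3% | 87.7% |
| 5 | **220** | 95.0% | 92.7% | 85.0% |
| 6 | 232 | 93.8% | 91.1% | 82.5% |

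The 220 is arithmetically correct for its inputs, and only at 5 df. The column for 160 is the recruitment goal less the missing-data limit: 200 × (1 − 0.20) = 160.

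**2. Look for a 5-df comparison.** A two-way table has (rows − 1) × (columns − 1) df. The groupings the article describes give:

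- frontline versus second-line, binary outcome: 1 × 1 = 1
- frontline versus second-line, three-level outcome: 1 × 2 = 2
- four professional categories, binary outcome (or by exposure): 3 × 1 = 3
- four professional categories, three-level outcome: 3 × 2 = 6

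None gives 5.

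**3. What the planned size detects in the named regression.** The article gives no regression effect size or predictor count, so these are assumptions: a test of one coefficient, 10 to 15 predictors (k), one observation per person, two-sided alpha 0.05.

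Formula: power = P(F(1, n − k − 1, λ) > the 95th percentile of the central F), with λ = f² × n. The partial correlation is r = √(f² / (1 + f²)).

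| n | f² (80% power) | partial r | f² (95% power) | partial r |
|---|---|---|---|---|
| 220 | 0.036 | 0.19 | 0.060 | 0.24 |
| 200 | 0.040 | 0.20 | 0.066 | 0.25 |
| 160 | 0.050 | 0.22 | 0.082 | 0.28 |

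For example, at n = 200 and 80% power, √(0.0396 / 1.0396) = 0.195. To these decimals, 10 and 15 predictors give the same result.

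**4. Power over a range of assumed effects** (one coefficient, 10 predictors).

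| f² | n = 220 | n = 200 | n = 160 |
|---|---|---|---|
| 0.02 | 55% | 51% | 43% |
| 0.05 | 91% | 88% | 80% |
| 0.09 | 99% | 99% | 96.5% |

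Regression power at these sizes runs from about 43% to 99%, depending on an effect that the article does not state.

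**The case against.** Much of the case on the other side stands.

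- **The 5 df are inferred.** The article does not state them. Another route to 220 exists: 3 df with 15% added, 191 × 1.15 = 219.65, rounded up to 220. Against this, the section presents 220 as the program's output and mentions no inflation. Whatever the df, w is not a regression effect size.
- **A reader might infer that the study never runs a chi-square test.** That cannot be shown. This is a condensed article, a separate analysis plan may exist, and objectives I and II name no test. A binary outcome across six age or experience bands would have 5 df. What can be said is that no such comparison is described.
- **A reader might infer that the Discussion flatly contradicts the 95% figure.** It denies only that a specific primary hypothesis was powered. A generic calculation at a chosen w can coexist with that, and the Sample Size section also cites feasibility, cost and logistics. The two passages are in tension, not in strict contradiction.
- **A reader might infer that the study is underpowered.** The numbers do not support this. At w = 0.3, 220 gives more than 95% power at 1 to 4 df, and 200 still does at 1 to 3 df. In the regression, moderate effects are well covered; low power appears only if small effects are assumed.
- **The regression figures rest on assumptions.** The predictor count is not in the article, 160 is the limit of the missing-data target, and three assessments per person are planned, which the calculation ignores.

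The mismatch survives all of this: the one stated power figure is not tied to the one stated analysis, nor to the stated recruitment goal.

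**Conclusion.** The point holds as a mismatch between calculation and analysis. The 220 is correct for its inputs, but the test and df are missing, the df implied by the arithmetic (5) fit no comparison described, and the 95% does not apply to the linear regression of objective III. Nor is it the power at the planned size: at 5 df it falls to 92.7% at 200 and 85.0% at 160.

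For one regression coefficient, the planned size detects a partial correlation of about 0.20 to 0.22 with 80% power and 0.25 to 0.28 with 95% power, under the assumptions stated above.

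The severity is moderate to low. The study calls itself exploratory, and neither the design nor any estimate changes. The correction matters because it stops the 95% figure from being used to interpret null associations.

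**What to change.** In the Sample Size section:

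1. Remove the w = 0.3, 95% power statement as the justification for the size. Alternatively, keep it labelled as an indicative chi-square calculation, name its test and df, and restate its power at the planned 200.
2. Add the effect detectable for one regression coefficient at the planned size, with its assumptions (about 10 to 15 predictors, one observation per person, two-sided alpha 0.05). For 80% power this is a partial correlation of about 0.20 at 200 and 0.22 at 160; for 95% power, 0.25 and 0.28.
3. Keep the Discussion's exploratory statement, and make the recruitment goal, the Sample Size section and the Discussion agree on the planned number and on what it was chosen for.

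The cost is rewording one paragraph. The downside is that the stated figure becomes less favourable. No extra participants are needed.
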